### Educational intervention

The main tool for the implementation of the intervention is a website designed by experts in the field of Health Education, and which has been adapted for Spain (http://www.alertagrumete.com) and Mexico (http://www.alertagrumete.com.mx).

In a previous stage, a qualitative research into a focal group formed by Spanish students was carried out in order to find out their likes and preferences. The result was a website with an animated interface and bright colors, and which is inspired on pirates. Users are identified with a captain who fights to avoid the boarding of the ship by a crab, which symbolizes cancer (Additional file 1 and Figure 2). The contents and aims of each section of the website are summarized below:

•*Challenge chest*. This is the most important area from an educational standpoint. Every week during the academic year, students are provided with a challenge or problem to be solved, which is adapted (a) to their curriculum, (b) to their educational level and (c) to cancer prevention. The challenges were devised by Secondary Education teachers who had previously attended a training course about Health Education. The main aim of the challenges is to impact positively on students’ attitudes and self-efficacy, as well as to encourage them to follow ECAC advice. An example of a simple challenge addressed to the youngest pupils is the following: ‘*Tobacco and potato plants can be cultivated on the same field*. *If four million hectares of tobacco were replaced by potato plants*, *how many millions of tons of the latter could be harvested to reduce hunger in the world*, *having in mind that in one square meter an average of 10 kg of potatoes could be collected*? *Correct answer*: *400 million tons*’.

•*Diet Analysis*. Diet experts perform different tasks. They: (a) analyze recipes, (b) collect 24-hour food recalls sent by the students, and (c) provide online dietary advice. Its main target is to achieve a positive attitude towards preventive diets, while highlighting their many advantages.

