The obtained information allows us to design the ‛*main result variable*’, which is a synthetic indicator of the percentage of cancer risk in each individual based on his/her risk behaviors (i.e., the so called ‛global cancer behavioral risk’). This indicator is calculated by simply adding up all the risk points obtained by each person when he/she did follow the ECAC advice (Table 2); that means that a scoring of 100 shows the maximal behavioral cancer risk. These risk points are obtained from the percentage of responsibility for cancer, and according to scientific evidence, every behavior of the participant is responsible for this percentage [5-7,30,31]. To know if the individuals are following or not the advice, we will (a) apply the stages of change pointed out by Prochaska and DiClemente to each behavior and we will (b) use a questionnaire of frequency of food intake (regarding both risk foods and cancer protective foods). This questionnaire also includes information related to many variables, which according to scientific literature could modify the effect, since they influence the following (or lack of following) of the ECAC advice. These variables are: (a) *socio*-*demographic variables* (e.g., age, gender, country of residence – Spain or Mexico –, cohabitation, number of siblings, academic level, academic level of parents, weekly expenses, among others), (b) *family history of cancer* and (c) *determining factors of the A*.*S*.*E*. *Model* (i.e., social influence and self-efficacy for each behavior). Other variables which are related to the educational intervention are also controlled (e.g., SMS delivery, score obtained in the competition, number of months that the student is registered in the website, etc.).

**Table 2 T2:** **How to calculate the indicator**: “**total cancer behavioral risk**” (**principal result variable**)

**Cancer behavioral risk**	**Points**
Smoking	35
Not eating five servings of fruit and vegetables per day	20
Eating three or more daily fatty foods	10
Quotient “frequency of protection food/risk food” ≤0.9	8
Obesity/Overweight	15/10
Excessive drinking	5
Sedentary	5
Ultraviolet radiation exposure without protection	2
Workplace exposure to carcinogens*	5
Maximum punctuation in adolescents	100^†^

*Only in adults. ^†^ 105 points in adults.

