The statistical analysis will be performed through multivariate regression procedures (using the ‘Enter’ method) to control the effect of potential confounders and modifiers of the effect. Regressions will follow several steps in order to establish the percentage of variability of the result variable which is explained by the remaining variables.

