## Discussion

In this section we aim to discuss the main features of the methodological design of Prevencanadol:

Firstly, the project complies with the basic requirements for a parallel randomized controlled trial: (a) the study factor is artificially manipulated (online educational intervention and delivery of SMS) and (b) the study population is randomly distributed to an EG and to a CG. Notwithstanding that, this randomization is determined by the first registered student of a classroom, and consequently real classroom randomization is achieved. From this standpoint, this trial can be considered a cluster randomized controlled trial, which is a very useful design to avoid the possible contamination of the groups. However, an important limitation of the experimentation with educational interventions is that it is not possible to guarantee that participants have received the content of the intervention, as it could be done if it were a pill, for instance. But Prevencanadol has managed to reduce this limitation since it has incorporated in the statistical analysis the scoring obtained during the competition, which is an indirect indicator of the reception degree of the intervention.

Secondly, as already pointed out, the program addresses a target population between 12 and 16 years old in order to reach the highest cancer preventive efficacy, since adolescence is a vital stage in which many behaviors (that will shape the adult stage) are acquired and consolidated. Although it can be a difficult age range, prevention of risk behaviors in this population group is also possible, especially if advice is linked to the school context [32-34]. However, it is not a task that is exclusively linked to school: we should bear in mind that society and family can be important sources of behaviors [35], and therefore we also encourage the registering of adults (teachers and family) in the website http://www.alertagrumete.com. In this way, it is even possible that healthy adolescents also become instigators of some preventive behaviors among adults; that consequently achieves ascending education. Finally, regarding the diversity of participants, we should also mention that we could only have included in the program adolescents with established risk behaviors, as other authors do in their works [36], but in our opinion when working with such a young population, it is as necessary to treat existing risk behaviors as well as to prevent their presence.

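### Competition score and SMS delivery arise after allocation yet are controlled in the regression, and no step without them is named as the effect estimate

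*Protocol article*

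**What the plan says.** All references are to the protocol article.

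- *Assessment of the impact of the intervention* lists the questionnaire covariates: socio-demographic variables, family history of cancer, and the A.S.E. determinants, given as "social influence and self-efficacy for each behavior". It describes them as variables "which according to scientific literature could modify the effect, since they influence the following (or lack of following) of the ECAC advice".
- The same section then adds: "Other variables which are related to the educational intervention are also controlled". Its examples are SMS delivery, the competition score and the number of months registered.
- The analysis is by "multivariate regression procedures (using the ‘Enter’ method) to control the effect of potential confounders and modifiers of the effect". The regressions proceed in several steps, whose stated purpose is to find how much of the outcome's variability the other variables explain.
- The *Discussion* concedes that receipt of an educational intervention cannot be guaranteed. It says the programme reduces this limitation "since it has incorporated in the statistical analysis the scoring obtained during the competition", and calls the score an indirect indicator of how much was received.
- *Aim* gives the main objective as assessing the impact of the intervention.

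**The concern.** A covariate can be added to a randomised comparison without changing what the arm coefficient means only if allocation cannot have affected it. Competition score and SMS delivery fail that condition. They record how much of the intervention a participant took up or was sent. Holding them fixed asks what allocation does among people with equal uptake, which is not the impact named as the main aim.

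Two distortions follow. The part of the benefit that works through participation is taken out of the arm coefficient. In addition, pupils in different arms with the same score are likely to differ in motivation. If motivation also lowers risk behaviour, the comparison is confounded in a way randomisation no longer prevents. A real benefit may look small, absent or harmful, and a null intervention may appear to have an effect.

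**Working it through.** **Step 1. Are the variables post-allocation?**

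- *Intervention procedure* puts registration and the pre-test first, then assignment. Points for site activities therefore come after assignment.
- The same section gives controls limited access and the experimental group (EG) all activities, with points coming chiefly from the challenges. Arm therefore drives the score.
- The *Discussion* defines the manipulated study factor as the online education together with SMS delivery. Controlling for SMS delivery conditions on a component of the treatment.
- *Study population and composition of the groups* makes a mobile phone optional, so SMS delivery can also vary with phone ownership.
- Months registered depends largely on the registration date, which precedes assignment, so I do not count it here.

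**Step 2. What of the A.S.E. determinants?** The same questionnaire is completed at pre-test and post-test, so both sets of values exist. Pre-test values are ordinary baseline covariates. Post-test values could be mediators. "The main aim of the challenges is to impact positively on students" begins the statement of the challenges' purpose, which goes on to name attitudes and self-efficacy. The SMS also aim at self-efficacy. Social influence is a target of the library, videos and forum. The article does not say which time point enters the model.

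**Step 3. How far can the coefficient move?** The article has no figure of its own to reproduce on this point. With the score in a linear model:

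adjusted arm effect = T - b × D

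Here T is the total effect, D the difference in mean score between arms, and b the pooled within-arm slope of outcome on score.

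From the article: 60% control allocation, and T = -10, set to the decrease used for the sample size. Everything else is assumed:

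- n = 1,000, residual SD 15, 400 replicates, no clustering.
- Mean exposure 1.0 in EG and 0.2 in control, so D = 0.8.
- Within-arm exposure SD 0.5 (EG) and 0.25 (control), with half the variance due to motivation.
- The score equals exposure, or exposure plus noise of SD 0.5.
- Motivation lowers risk by c points per SD.
- P is the part of T that runs through participation.

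Pooled within-arm variance of exposure = 0.4 × 0.25 + 0.6 × 0.0625 = 0.1375.

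Pooled covariance with motivation = 0.4 × 0.3536 + 0.6 × 0.1768 = 0.2475.

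Ratio = 0.2475 / 0.1375 = 1.80, and 1.80 × 0.8 = 1.44.

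So b × D = λ(P - 1.44c), with λ = 1 for an exact score and λ = 0.1375 / (0.1375 + 0.25) = 0.355 for the noisy one. The adjusted effect is -10 - λ(P - 1.44c).

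| Scenario | Formula | Simulated, arm only | Simulated, arm + score |
|---|---|---|---|
| P = 0, c = 0 | -10.00 | -10.02 | -9.93 |
| P = -10, c = 0, noisy score | -6.45 | -9.99 | -6.50 |
| P = -5, c = 0 | -5.00 | -10.01 | -4.98 |
| P = -10, c = 3, noisy score | -4.92 | -9.95 | -4.87 |
| P = 0, c = 5 | -2.80 | -10.13 | -2.97 |
| P = -5, c = 3 | -0.68 | -9.99 | -0.66 |
| P = -10, c = 0 | 0.00 | -10.05 | -0.08 |
| P = -5, c = 5 | +2.20 | -9.94 | +2.25 |
| P = -10, c = 3 | +4.32 | -9.94 | +4.45 |
| P = -10, c = 5 | +7.20 | -10.06 | +7.07 |

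Formula and simulation agree to within 0.2. Arm alone recovers -10 throughout. With T = 0 and P = 0, the exact-score formula gives +1.44c, so c = 3 produces an apparent harm of 1.44 × 3 = 4.32 points from an inert intervention.

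**The case against.** The strongest defence is that the article does not commit to one simultaneous model. It speaks of several steps, and the Enter method may apply within each. An early step could hold arm and baseline variables, with score and SMS added later. The Discussion also gives the score a dose purpose, which is legitimate in a secondary analysis. The full protocol or analysis plan, not shown, may settle the order. This stands as far as it goes: a single model holding everything is an inference. But the article does say these variables are controlled and presents that as a strength. The stated purpose of the steps is explained variability, and no step free of these variables is singled out as the effect estimate. That is a stated choice, not detail left for later.

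A reader might infer three stronger things, none of which the document supports:

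- **That the adjustment is bound to remove or reverse the effect.** The table shows that shrinkage is just as possible, and that nothing is lost when the score is unrelated to outcome. That last case, however, would undercut the reason for including the score.
- **That the A.S.E. determinants are products of the intervention.** They are also measured at pre-test, and their timing in the model is simply not stated.
- **That the simulated values measure the bias in this trial.** Score distributions, outcome SD and the influence of motivation are all assumed. Control access is limited, not absent, and points are also given for questionnaires.

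**Conclusion.** Wrong as written, for competition score and SMS delivery. Any regression step that includes them gives an arm coefficient that is not the effect of allocation, and the article names no other step as its main result. This conclusion rests on the article's own account of when points are earned, who has access, and what the randomised factor comprises. It does not rest on the simulation.

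The size is unknown. Under the assumed inputs, a true -10 became anything from about -10 to +7. The result depends on how much of the effect runs through participation, how well the score measures participation, and how strongly unmeasured motivation acts.

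For the A.S.E. determinants, the finding is only that the time point needs stating. I treat pre-test values as baseline. For a pupil joining a classroom whose arm is already set, the pre-test precedes that pupil's own access but not the classroom's allocation.

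**What to change.** In *Assessment of the impact of the intervention*:

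1. State that the primary analysis compares the randomised groups, using arm plus baseline covariates only. These would include the pre-test risk score, age, gender, country and pre-test A.S.E. values. Name this step as the source of the effect estimate.
2. Remove competition score, SMS delivery and any post-test A.S.E. values from that model.
3. Place them in a separate, labelled secondary analysis: dose-response within the EG, presented as observational; a complier average causal effect with allocation as instrument, stating the assumption that allocation acts only through participation; or a mediation analysis.
4. Reword the *Discussion* so that the score supports this secondary analysis and not the main comparison.

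The cost is analysis wording only. No new data are needed, because the questionnaire is already completed before and after the intervention.

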## Abbreviations

ECAC: European Code Against Cancer; SMS: Short Text Message/Short Message Service; EG: Experimental group; CG: Control group.
